# Comparing efficacy and safety between Naldebain^**®**^ and intravenous patient-controlled analgesia with fentanyl for pain management post-laparotomy: study protocol for a randomized controlled, non-inferior trial

**DOI:** 10.1186/s13063-019-3260-4

**Published:** 2019-03-18

**Keywords:** Efficacy and safety, Naldebain^®^, Fentanyl, Patient-controlled analgesia, Post-laparotomy

## Abstract

**Background:**

A long-acting prodrug of nalbuphine, nalbuphine sebacate, has been developed for meeting the unmet medical need of long-acting analgesics. Naldebain^®^ (nalbuphine sebacate) has been developed as a new premedication for postoperative pain management. The primary objective of this study is to determine the efficacy and safety of a single dose of intramuscular Naldebain^®^ in patients scheduled to undergo elective laparotomy.

**Methods/design:**

A total of 110 patients will be recruited and randomized into two treatment groups. Group 1 receives a single dose of Naldebain^®^ intramuscularly 24 ± 12 h prior to surgery. Group 2 receives intravenous patient-controlled analgesia (PCA) with fentanyl through 48 h postsurgery. Both groups will have follow-up observations until the final visit (day of discharge, day 6–30). The primary efficacy endpoint is to assess time-specific pain intensity calculated as the area under the curve (AUC) of a visual analog scale at individual time points and by using total AUC. Safety endpoints—including incidence of treatment, emergent adverse events, and percentage of abnormality from baseline to final visit—in vital signs, laboratory tests, and injection site evaluations will also be analyzed. Statistical analyses will be performed on the data to compare the two groups.

**Discussion:**

Post-laparotomy pain can have a harmful effect on patient recovery; therefore, a slow-release formulation that can cover at least 7 days of analgesic effect is required. This study will demonstrate whether a single use of Naldebain^®^ is not less efficacious than PCA with fentanyl for pain management as a non-inferior trial.

**Trial registration:**

NCT03296488.

**Electronic supplementary material:**

The online version of this article (10.1186/s13063-019-3260-4) contains supplementary material, which is available to authorized users.

## Background

### Disease background

Most patients who undergo surgery experience acute postoperative pain; however, evidence suggests that fewer than half of the patients achieve adequate or satisfactory postoperative pain relief [1]. Postoperative pain, especially when poorly managed, leads to harmful acute effects (i.e., adverse physiological responses) and increases the risk of postoperative complications and persistent postoperative pain [2]. Persistent postoperative pain is an intricate response to tissue trauma during surgery that stimulates hypersensitivity of the central nervous system, which causes pain in areas not directly affected by the operative procedure. Either acute or chronic postoperative pain can increase the possibility of postoperative complications, increase the cost of medical care, and complicate wound recovery and subsequent return to normal activities. Pain control following surgery is a major priority for both patients and surgeons.

Several preoperative, intraoperative, and postoperative interventions and management strategies are available for reducing and managing postoperative pain. Opioids and nonsteroidal anti-inflammatory drugs (NSAIDs) are commonly used for postoperative pain management [3]. When given systematically, however, these drugs cause side effects including nausea, vomiting, dizziness, sedation, and pruritus [4]. Opioids can cause respiratory depression, and NSAIDs can impair renal function [5].

### Investigational product

Naldebain^®^ (150 mg nalbuphine sebacate, 75 mg/mL, 2 mL/vial), developed by Lumosa Therapeutic, Inc. (Taipei, Taiwan), is a new premedication for postoperative pain management.

### Rationale

A long-acting prodrug of nalbuphine, nalbuphine sebacate, has been developed for meeting the unmet medical need of long-acting analgesics. Nalbuphine sebacate (Naldebain^®^) is formed by the esterification of two equivalents of nalbuphine with one equivalent of sebacoyl chloride. According to preclinical animal studies, the median lethal dose value of nalbuphine sebacate is considered to be 300 mg/kg for dogs following a single intramuscular administration of nalbuphine sebacate oily solution. The no observed adverse effect level is considered to be less than 30 mg/kg in dogs. In humans, several clinical studies have been conducted to investigate the pharmacokinetics, bioavailability [6–8], efficacy, and safety of Naldebain^®^. The currently proposed clinical use of nalbuphine sebacate is a single dose of Naldebain^®^ administered intramuscularly approximately 24 h prior to the planned surgery for pain relief.

#### Objectives

The primary objective of this study is to determine the safety and efficacy of a single dose of intramuscular Naldebain^®^ administered preoperatively to patients scheduled to undergo elective laparotomy compared with the safety and efficacy of patient-controlled analgesia (PCA) with fentanyl. The study will demonstrate whether a single use of Naldebain^®^ is less efficacious or not than PCA with fentanyl.

For the evaluation of efficacy, the primary endpoint was defined as follows: the area under the curve (AUC) of visual analog scale (VAS) pain intensity scores through 48 h following surgery. The secondary endpoints were as follows: 1) the total consumption (mg) of supplemental analgesics administered postsurgery; 2) pain assessment calculated as the AUC of VAS pain intensity scores from the end of surgery through day 6; 3) pain intensity and interference of the brief pain inventory (BPI); 4) patient satisfaction on a five-point scale; and 5) length of postoperative hospital stay.

For the safety evaluation, two points were considered: 1) the incidence of treatment-emergent adverse events (TEAE); and 2) the abnormality percentage change from baseline to the final visit for vital signs, laboratory tests, and injection site evaluations.

## Methods and design

### Overall design

A randomized, positive-controlled, single-dose, parallel-design study will be conducted with 110 male and female patients scheduled to undergo elective laparotomy to assess the safety and efficacy of an intramuscular injection of Naldebain^®^. The study was designed to include a 5% dropout rate as taken from a previous published work [8].

A total of 110 eligible hospitalized patients will be randomized into one of two treatment groups in a 1:1 ratio. Group 1 is the intramuscular Naldebain^®^ (IM-Naldebain^®^ group) and Group 2 is the intravenous PCA with fentanyl (IV-PCA group). Group 1 receives a single dose of Naldebain^®^ (150 mg nalbuphine sebacate) intramuscularly 24 ± 12 h before surgery. Group 2 receives intravenous PCA with fentanyl through 48 h postsurgery. If PCA with fentanyl is deemed unnecessary by both investigator and patient, the PCA machine can be removed prior to the completion of 48 h as required. If patients require additional medication for treatment of pain, ketorolac and morphine can be used as supplemental analgesics as required. Both groups will undergo follow-up observation until the final visit (from the day of discharge through day 6–30). Statistical analyses will be performed on the data to compare the two groups.

### Number of patients and randomization

Assuming an equivalence margin of 10 and a standard deviation of 18 [8], 104 patients are required to achieve 80% power using the non-inferiority test with a one-sided 97.5% confidence interval (equivalent to a two-sided 95% confidence interval). A total of 110 eligible patients will be randomized in this study, with a predicted dropout rate of 5%. The participants will be randomized using sealed, opaque, individually numbered envelopes, with a restriction of selecting one per person. The envelopes contain data sheets with information on group allocation and the randomization number, generated by the statistician with SAS software. A randomization schedule stratified by center has been prepared. The schedule links sequential numbers to treatment codes allocated randomly. The schedule was prepared with a 1:1 block randomization ratio.

Eligible patients will be randomized to the study medication in accordance with the randomization schedule. The next eligible patient will receive the study medication with the lowest available randomization number. Patients will be only given the study medication carrying their randomization number.

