#### VAS and patient diary

The VAS is a 10-cm numeric scale (0 = no pain to 10 = worst pain ever).

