### Data management and statistical methods

#### Study endpoints

The following endpoints will be evaluated.

The primary efficacy endpoint is the pain assessment (time-specific pain intensity) calculated as the AUC of VAS pain intensity scores through 48 h postsurgery.

The secondary efficacy endpoints are as follows: 1) the total consumption (mg) of supplemental analgesics administered postsurgery; 2) pain assessment calculated as the AUC of VAS pain intensity scores from the end of surgery through day 6; 3) pain intensity and interference of BPI; 4) patient satisfaction on a five-point rating (Table 2); and 5) length of postoperative hospital stay.

The safety endpoints are as follows: 1) incidence of TEAE; and 2) percentage of abnormality from baseline to final visit in vital signs, laboratory tests, and injection site evaluations.

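### The non-inferiority margin of 10 and SD of 18 have no unit or named endpoint, so the decision threshold is not fixed on the AUC0-48 scale that will be analysed

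*Protocol article*

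**What the plan says.** The only numerical margin in the protocol article is in *Number of patients and randomization*, where the sample-size statement reads: "Assuming an equivalence margin of 10 and a standard deviation of 18 [8], 104 patients are required to achieve 80% power". The method behind this figure is then given as "using the non-inferiority test with a one-sided 97.5% confidence interval (equivalent to a two-sided 95% confidence interval". One literature reference follows the two figures. The paragraph does not say what quantity they describe or in what unit. It then raises the total to 110 for 5% dropout.

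Two other sections define the scale on which the trial is judged. *VAS and patient diary* states: "The VAS is a 10-cm numeric scale (0 = no pain to 10 = worst pain ever". *Study endpoints* defines the primary efficacy endpoint as pain "calculated as the AUC of VAS pain intensity scores through 48 h postsurgery".

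*Efficacy analysis* computes the AUC by the trapezoidal method and compares the arms with a two-sample t test. It does not mention dividing by time and names no margin. *Hypotheses and level of significance* names no margin either.

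**The concern.** In a non-inferiority trial the margin is the decision rule. The upper limit of the confidence interval for the difference in AUC0-48 (Naldebain minus PCA) has to be set against a number on the same scale. The only number available is an unlabelled 10.

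The figures do not sit naturally on either scale that the protocol defines. As VAS scores on 0-10 they are impossible. As an undivided area over 48 h they are possible, but they imply patients who are almost uniform in average pain and a margin of about a fifth of a centimetre. The protocol enrols adults aged 20 to 80, ASA class 1 to 3, having any elective open laparotomy, with supplemental analgesia as needed, so such uniformity is hard to credit.

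Two things are at stake. The same result could pass or fail depending on the unit chosen. An upper confidence limit of 30 cm·h, for example, fails against 10 cm·h and passes against 48 cm·h. The stated 80% power also carries over to the primary endpoint only if that endpoint's SD really is 18 in the margin's unit.

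**Working it through.** **Inputs from the protocol.** Margin 10 and SD 18 (no unit); one-sided 0.025; power 80%; 1:1 allocation; 5% dropout; VAS 0 to 10; AUC over 48 h. **Assumed:** a true difference of 0, which the protocol does not state.

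**1. Reproduce the stated sample size.** Normal approximation: n per arm = 2 × (1.96 + 0.8416)² × 18² / 10² = 50.9, so 51 per arm, 102 in total. With the noncentral t distribution, 51 per arm gives 79.3% power and 52 per arm gives 80.1%, so 52 per arm, 104 in total, exactly as stated. Dropout: 104 / 0.95 = 109.5, so 110. All the stated figures are reproduced.

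**2. Could the figures be scores on the 0-10 VAS?** The largest SD on a 0-10 scale is half the range, 5, reached when half the patients score 0 and half score 10. An SD of 18 is impossible, and a margin of 10 would be the whole scale. The same holds for a time-averaged score.

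**3. Could they be AUC0-48 in cm·h?** The range is 0 to 10 × 48 = 480 cm·h, so both figures are possible. Divided by 48 h:
- margin: 10 / 48 = 0.21 cm of average pain, and 10 / 480 = 2.1% of the range
- SD: 18 / 48 = 0.375 cm of average pain

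If average pain is roughly normal, about 95% of patients would lie within 1.96 × 0.375 = 0.74 cm of the mean.

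**4. Alternative reading (assumption): mm of average pain on a 0-100 scale.** The margin is 10 mm = 1.0 cm, so 1.0 × 48 = 48 cm·h. The SD is 18 mm = 1.8 cm, so 1.8 × 48 = 86.4 cm·h. The ratio of thresholds is 48 / 10 = 4.8.

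**5. Does the unit alone change the power?** No. Power depends on margin/SD, which is 10/18 = 48/86.4 = 0.556. At 52 per arm it is 80.1% under both readings.

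**6. What if the SD of the endpoint is not 18 in the margin's unit?** Power at 52 per arm, for assumed SDs of 48-h average pain:

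| Assumed SD of average pain (cm) | SD of AUC0-48 (cm·h) | Power, margin 10 cm·h | Power, margin 48 cm·h |
|---|---|---|---|
| 0.375 (literal 18 cm·h) | 18 | 80.1% | about 100% |
| 0.5 | 24 | 55.7% | about 100% |
| 1.0 | 48 | 18.2% | 99.9% |
| 1.5 | 72 | 10.4% | 92.0% |
| 1.8 | 86.4 | 8.5% | 80.1% |
| 2.0 | 96 | 7.6% | 71.4% |

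At an SD of 86.4 cm·h the 95% confidence interval has a half-width of about 1.96 × 86.4 × √(2/52) = 33.2 cm·h. That is more than three times a margin of 10 and well inside a margin of 48.

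**The case against.** The strongest reply is that the arithmetic is right. A reader might infer from the missing unit that the 80% power is unsupported. The documents do not bear that out: the stated inputs give 104 patients and 80.1%, and a unit shared by both figures cancels. A reader might also infer that the trial has almost no chance of success if the margin is applied literally. That is not the literal reading. Taken literally, both figures are in cm·h and power is 80.1%. The low values appear only when the protocol's SD is replaced by an assumed one while the margin stays at 10 cm·h. This part of the objection stands.

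It is also fair that 10 and 18 lie inside the 0 to 480 range. No AUC SD is given anywhere, and no section mentions a 0-100 mm scale. *Implausibly small* is therefore a judgement, and the factor 4.8 depends on an assumed source scale. In mm·h, a margin of 10 would be 1 cm·h, a 48-fold difference from the mm-score reading. That makes the uncertainty wider.

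Finally, this is a journal article, and the full protocol or analysis plan may give the unit. If so, the correction is one line. But the article itself states the margin and SD, in a form that cannot be scores on its own VAS and is doubtful as its own AUC. This is more than a detail left to another document.

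**Conclusion.** The concern holds for the decision threshold. The only margin in the protocol has no unit and no endpoint, cannot be a score margin on the VAS as defined, and corresponds to just 0.21 cm of average pain if read as AUC0-48 in cm·h. As written, it cannot be applied to the primary endpoint without choosing a unit. Under the two readings worked through, the threshold is 10 or 48 cm·h. The second rests on the assumption that the source figures are mm on a 0-100 scale.

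The sample-size calculation itself is not in error. The 80% applies to the endpoint analysed if, and only if, its SD is 18 in the margin's unit, and the documents cannot settle that. If the margin is 10 cm·h and the SD of average pain is between 0.5 and 1.8 cm (assumed), power lies between 56% and 8.5%. If the figures are mm scores, 110 patients and 80% power stand unchanged.

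**What to change.** In *Number of patients and randomization*:
- State the unit, scale and endpoint of both the margin and the SD.
- Express both on the scale that will be analysed: AUC0-48 in cm·h, or AUC divided by 48 as time-weighted average VAS in cm. Name the same scale in *Efficacy analysis*.
- Confirm that the SD taken from the cited study is for that quantity. If it is not, restate the power with an SD that is. The pooled SD of enrolled patients, ignoring arm, can serve as a check.

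If the source figures prove to be 0-100 mm scores of average pain, the entry would be a margin of 1.0 cm (48 cm·h) and an SD of 1.8 cm (86.4 cm·h), with 110 patients kept.

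This has to be settled before any by-arm comparison. *Trial status* expected completion in December 2018 and the article is dated March 2019. If the arms have already been compared, the unit should be taken from a document dated before that comparison, and this should be disclosed.

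The cost is a change of wording. No extra patients are needed to correct the statement. The downside is that the stated power may turn out less favourable.

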##### Study day 1 (all eligible patients)

Eligible patients are required to check into the clinical site before surgery (day 0). The following procedures are performed at check-in: 1) review inclusion/exclusion criteria; 2) randomization; 3) review of concomitant medications; and 4) review of adverse events (AEs).

Additional laboratory tests are requested as required by the investigator.

All eligible patients are hospitalized and randomized into the two treatment groups: Group 1—intramuscular Naldebain^®^ (150 mg nalbuphine sebacate) 24 ± 12 h before surgery; Group 2—Intravenous PCA with fentanyl through 48 h postsurgery.

For pain assessment, patients in Groups 1 and 2 rate their pain intensity using the VAS pain scale prior to dosing or at day 1, respectively.

Vital signs are checked prior to dosing and once daily until day 6.

Group 1 receives Naldebain^®^, and the injection site is evaluated within 1 h prior to dosing.

##### Study day 0 to 5

All patients are given general anesthesia prior to their scheduled surgical procedure. If patients require additional medication for the treatment of pain, ketorolac and morphine can be used as supplemental analgesics as required. Post-surgery, the following evaluations are performed: 1) for pain assessment, all patients rate their average pain intensity using a VAS pain scale (assessments are performed before the first use of PCA or supplemental analgesics and then at 4 ± 1, 24 ± 2, 32 ± 3, and 48 ± 4 h, and once daily on day 3 to day 5 following surgery); 2) BPI evaluation is performed on day 2; 3) vital signs (temperature, respiratory rate, blood pressure, and heart rate) are examined once daily prior to the final visit; 4) in Group 1 (the IM-Naldebain^®^ group), the injection site is evaluated once daily until the final visit; 5) a review of concomitant medication and adverse events are record; and 6) in Group 2 (the IV-PCA group), the amount of fentanyl used is recorded from day 0 through day 2.

##### Study day 6

The following evaluations are performed at day 6: 1) for pain assessment, patients rate their pain intensity in the patient diary; 2) BPI is evaluated; 3) vital signs (temperature, respiratory rate, blood pressure and heart rate) are examined; 4) the injection site is evaluated; 5) a review of the AE record; and 6) a review of concomitant medication.

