#### Hypotheses and level of significance

Statistical analyses will be performed on the data to compare the Naldebain^®^ group with the PCA group. All statistical tests will be two-sided and evaluated at a level of significance of 0.05.

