#### Efficacy analysis

Pain intensity will be analyzed at individual time points and by AUC. The mean AUCs at 0–24 h and 0–48 h for Naldebain^®^ and PCA will be calculated using the trapezoidal method. These values will then be compared using a two-sample *t* test.

For total postsurgical consumption of supplemental analgesics, opioid and NSAIDs will be counted separately. A two-sample *t* test will be used to compare treatment groups. Between-group differences at baseline in answers to BPI questions based on rating scales will be analyzed using a two-sample *t* test; an analysis of covariance model will then be used for postsurgical BPI assessments with baseline response as the covariate. A chi-square test will be used to compare the Naldebain^®^ and PCA groups with respect to patient satisfaction with postsurgical analgesia. Length of postoperative hospital stay will be tested using a two-sample *t* test.

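### The primary AUC comparison uses neither the centre stratification nor the preoperative VAS score; any error is conservative, and the gain from adjusting is uncertain and may be small

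*Protocol article*

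**What the plan says.** All references are to the protocol article.

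- **Allocation** (Number of patients and randomization): "A randomization schedule stratified by center has been prepared", in 1:1 blocks. The number of centres is not given.
- **Baseline pain** (the check-in visit, headed Study day 1): the two groups "rate their pain intensity using the VAS pain scale prior to dosing or at day 1, respectively". Table 1 puts this pain assessment in the day −1 column together with randomization, so I read it as a preoperative rating in both groups.
- **Primary analysis** (Efficacy analysis): AUCs over 0–24 h and 0–48 h are obtained by the trapezoidal rule, and then: "These values will then be compared using a two-sample" t test. No centre term and no covariate are named.
- **Other endpoints**: the same section plans ANCOVA with the baseline response for postsurgical BPI. The Safety analysis section adjusts changes in laboratory values and vital signs for baseline. Centre otherwise appears only as a breakdown in descriptive safety tables.
- **Sample size** (in the same section as the allocation): the calculation reads "Assuming an equivalence margin of 10 and a standard deviation of 18 [8], 104 patients are required to achieve 80% power". The level is one-sided 2.5%, which agrees with the two-sided 0.05 under Hypotheses and level of significance.

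**The concern.** Blocked allocation within centre keeps the arms nearly balanced in each centre, so differences between centres largely cancel from the treatment difference. A t test that ignores centre still counts those differences as noise, so its standard error is too large whenever centres differ. Baseline VAS is another matter: it is not a stratification factor, and omitting it only forgoes whatever variance it could explain.

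The non-inferiority conclusion depends on one confidence limit set against the margin. An interval wider than necessary therefore counts directly against the test product, in a trial planned at 80% power with little slack. The protocol already adjusts several less important outcomes for baseline and gives no reason for treating the primary endpoint differently.

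**Working it through.** **Inputs from the protocol article.** Margin 10, SD 18 (units not stated; only their ratio matters here), one-sided 2.5%, power 80%, 104 evaluable, 110 randomized, 1:1 allocation. The true difference is taken as 0.

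**Inputs that must be assumed.** The share R² of AUC variance explained by centre and/or baseline VAS, and the number of centres. The documents give neither, nor any correlation between preoperative VAS and the AUC.

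**1. Reproduce the plan's figure.** The normal approximation n = 2(1.96 + 0.842)² × 18²/10² gives 51 per arm, or 102 in total. With the noncentral t distribution, 51 per arm gives 79.3% power and 52 per arm gives 80.1%, hence 104. Then 104/0.95 = 109.5, so 110. The stated figures reproduce for an unadjusted comparison.

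**2. Precision and power with adjustment.** Residual SD = 18 × √(1 − R²). Half-width = t(0.975) × residual SD × √(2/52). Power is from the noncentral t with 52 per arm.

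| R² (assumed) | Residual SD | 95% CI half-width | Power |
|---|---|---|---|
| 0 | 18.00 | 7.00 | 80.1% |
| 0.01 | 17.91 | 6.97 | 80.5% |
| 0.04 (correlation 0.2) | 17.64 | 6.86 | 81.7% |
| 0.10 | 17.08 | 6.64 | 84.1% |
| 0.20 | 16.10 | 6.26 | 88.0% |

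**3. Coverage when centre is left out.** Under stratification the true standard error is about √(1 − R²) times the one the t test estimates. The one-sided error is then about P(Z > 1.96/√(1 − R²)).

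- Centre share 5%: 1.96/0.975 = 2.01, error 2.2%, coverage 95.6%.
- Centre share 10%: 1.96/0.949 = 2.07, error 1.9%, coverage 96.1%.
- Centre share 20%: 1.96/0.894 = 2.19, error 1.4%, coverage 97.2%.

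Simulation used four equal centres, blocks of 4 and N = 104. With centre effects drawn at random (6,000 replicates), coverage was 95.5%, 96.0% and 96.4%, and one-sided error 2.3%, 2.0% and 2.0%. With centre effects fixed at exactly 10% and 20% of variance (20,000 replicates), coverage was 96.1% and 97.1%, and one-sided error 2.1% and 1.6%. Four randomly drawn centres realize less than the nominal centre variance, which mainly explains the gap. At a 2% share no effect was visible.

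**4. Coverage when only baseline VAS is prognostic.** With correlation 0.2 to 0.3, the simulated coverage of the unadjusted interval was about 95.1%, which is nominal.

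**5. Gain from centre alone.** The table overstates this, because stratification already makes the t test's estimate more precise. With fixed centre effects at 10% to 20% of variance, the unadjusted test has about 82% to 83% power, against 84% to 88% adjusted.

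**6. Cost if nothing is prognostic.** Simulated half-width was 7.03 adjusted and 6.99 unadjusted. Four extra degrees of freedom cost less than 0.1 percentage point of power.

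**The case against.** The strongest defence is that the design matches its test. The 104 evaluable patients were calculated for an unadjusted comparison, and the t test delivers the stated power on the stated inputs. Any miscalibration makes non-inferiority harder to claim, not easier. This stands.

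The centre argument also needs more than one centre. The article cites a single ethics approval and refers to one clinical site at check-in, although stratification and safety tables by centre suggest that several were intended. With one centre, that half of the point disappears. This stands as a condition.

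The benefit of baseline VAS is unproven. The rating is taken before elective surgery, and patients with chronic opioid use are excluded, so many scores may lie near zero and predict postoperative pain poorly. This stands too, and it is why the range above starts at 1%.

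A reader might infer that the primary endpoint is the only unadjusted one. It is not: supplemental analgesic consumption and length of stay are also compared by t tests, and satisfaction by a chi-square test. The inconsistency is narrower: the plan uses baseline where it has one for BPI, laboratory values and vital signs, but not for VAS.

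Nor can the choice be left to an unseen analysis plan as mere detail, because this document itself names the primary test.

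**Conclusion.** The point holds as a low-cost improvement to the analysis, not as an error that threatens the conclusion. The primary test ignores the trial's own stratification factor and a baseline measurement already collected.

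It is tempting to conclude that the confidence interval is simply too wide because neither variable is used. The documents do not support that. Over-coverage can come only from omitting centre, and only if several centres exist and differ; its size is about 95.5% to 97% for an assumed centre share of 5% to 20%. Omitting baseline VAS leaves the interval valid and at most less efficient.

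It is equally tempting to promise a large gain in power. The documents give no correlation or centre variance, so the honest range runs from essentially nothing to about 88% power at an assumed R² of 20%, with less to be had from centre alone. The trial is not underpowered by its own inputs, and type I error is not inflated.

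**What to change.** In the Efficacy analysis section, replace the t test for AUC0–48 with ANCOVA on treatment, centre (if there is more than one) and baseline VAS. State a rule in advance for pooling small centres. Compare the two-sided 95% confidence interval for the adjusted difference, Naldebain minus PCA, with the margin. Use the same model for AUC0–24 and the AUC to day 6, and keep the t test as a sensitivity analysis.

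Define baseline as the preoperative rating on day −1. The first rating after surgery cannot serve, because Group 1 has been treated by then. Type of surgery is recorded at screening but has no defined categories, so leave it out unless these are fixed in advance.

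The cost is a change of wording in the protocol and in any analysis plan that repeats it, plus a few degrees of freedom. No new data are needed. If the covariates prove unrelated to outcome, essentially no precision is lost. The model must be fixed before outcomes are compared by arm, so that the covariates cannot be chosen by their effect on the result.
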